### Participant timeline {13}

Patients scheduled for elective loop ileostomy closure are screened preoperatively (visit 1) (Fig. 1). Patients are enrolled given their ability to understand the extent and nature of the trial as well as their written informed consent after detailed patient information. All inclusion criteria and no exclusion criteria must be fulfilled. Baseline data are collected during screening/baseline visit. Included patients are randomised during surgery (visit 2). The ostomy closure will be performed as randomised. Follow-up visits will be on postoperative days 2–4, at discharge and on days 30–35 (visits 3–5) for evaluation of secondary endpoints. In addition, 12 and 24 months (visits 6–7) after surgery patients are planned for follow-up to evaluate primary and secondary outcome parameters. In case the patient is unable to attend clinical visits 6–7, a telephone evaluation will be performed. If the interview reveals a strong indication for the presence of an incisional hernia, the patient will be once again asked to present to the outpatient clinic for clinical and ultrasound evaluation. Protocol deviations will be assessed during the entire study period. An overview of the trial visits and collected data can be found in Table 3.

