#### Secondary outcome measures

Postoperative complications within 30 days according to the Dindo-Clavien classification (DCC) ≥3 [27]Number of surgical site occurrences (SSO) [28] defined as the sum of the following *individual* secondary endpoints:*Superficial or deep surgical site infections* (SSIs) within 1 year after index operation according to the CDC definition [29]. Follow-up for this endpoint will be 1 year as defined by the CDC in case of foreign body placement [29]. Organ-space SSIs are excluded in this measurement as they are independent of the abdominal wall closure technique, but rather depend on the underlying surgery. Furthermore, they are infrequent after ileostomy reversal. In addition, clinically relevant organ-space SSIs (defined as Dindo-Clavien ≥ grade 3) will be recorded in the overall complication rate according within 30 daysRate of *wound seromas* at former ostomy site within 30 days after index operation. Seroma will be defined as a collection of serous fluid in a dead space, which can either be in situ or leaking through a wound [30]. Assessment can be by clinical or radiologic examinationRate of *wound hematomas* at former ostomy site within 30 days after index operation. Hematomas are defined as an accumulation of blood in the wound area, which warrants (bedside) surgical exploration and intervention [31]*Enterocutaneous fistulas* within 24 months after index operation [28]Number of patients undergoing *incisional hernia repair* at the site of ileostomy closure within 24 months after the index operationNumber of *revision surgeries* because of complications related to ileostomy closure within 24 months after the index operation*Chronic postoperative pain* in the ileostomy closure site during follow-up measured via the Pain Questions of the modified EHS-QoL questionnaire at 12 and 24 months [32]*Health-related quality of life* at baseline, 12 and 24 months after index operation according to the EHS-QoL questionnaire [32]*Modified Hernia Recurrence Inventory (HRI)* at 12 and 24 months [26]

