### Adverse event reporting and harms {22}

Since trial interventions in P.E.L.I.O.N are medical routine, and the trial is conducted under the Medical Association’s professional code (Berufsordnung der Bundesärztekammer) §15, there is no need to record every adverse event. Instead of documenting serious adverse events (SAE), the following secondary endpoints will be used to assess safety in the P.E.L.I.O.N trial:Postoperative complications within 30 days according to the Dindo-Clavien classification (DCC) ≥3 [27]Superficial or deep surgical site infections (SSIs) within 1 year after index operation according to the CDC definition [29]Rate of wound seromas at former ostomy site within 30 days after the index operationRate of hematomas at former ostomy site within 30 days after the index operationEnterocutaneous fistulas within 24 months after the index operation [28]Number of revision surgeries because of complications related to ileostomy closure within 24 months after the index operation

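### The endpoints that replace SAE recording give non-operative closure-site complications after day 30 no explicit route, other than surgical site infection (to 1 year) and enterocutaneous fistula

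*Protocol article*

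**What the plan says.** Under Adverse event reporting and harms {22}, the protocol article states that "there is no need to record every adverse event", and continues: "Instead of documenting serious adverse events (SAE), the following secondary endpoints will be used to assess safety in the P.E.L.I.O.N trial". Six endpoints follow.

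Three of the six close at 30 days:
- major complications, "Postoperative complications within 30 days according to the Dindo-Clavien classification (DCC) ≥3";
- wound seroma, "at former ostomy site within 30 days after index operation. Seroma will be defined as a collection of serous fluid in a dead space", which may be found by examination or by imaging;
- wound haematoma, also to 30 days, defined as one "which warrants (bedside) surgical exploration and intervention".

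The other three run longer: "Superficial or deep surgical site infections (SSIs) within 1 year after index operation according to the CDC definition", enterocutaneous fistula to 24 months, and revision surgery for closure-related complications to 24 months.

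On visits, Participant timeline {13} says: "Follow-up visits will be on postoperative days 2–4, at discharge and on days 30–35 (visits 3–5) for evaluation of secondary endpoints". It then says: "In addition, 12 and 24 months (visits 6–7) after surgery patients are planned for follow-up to evaluate primary and secondary outcome parameters". Table 3 shows which secondary endpoints those later visits cover. Postoperative morbidity, seroma and haematoma are marked for visits 3–5 only.

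**The concern.** The arms differ by a permanent non-absorbable mesh. The description of the experimental operation also includes a dissected retromuscular space that the control description does not. A fluid collection or other closure-site complication that appears or persists after the first month is therefore a harm that could plausibly differ by arm.

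The protocol accepts this reasoning for infection: under Secondary outcome measures it sets a 1-year follow-up because that is the CDC rule when a foreign body is placed. It gives no matching reason for closing seroma and major complications at day 30.

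Efficacy is followed for 24 months, and the abstract says the result could make mesh the new standard. If late non-operative harms are not collected, the final balance of benefit and harm sets a 24-month benefit against a record of such harms that, apart from infection and fistula, covers about one month.

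**Working it through.** The plan gives no calculated figure on this point, so the check sets the endpoint windows against the visit schedule.

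**Step 1. Windows (Secondary outcome measures; Adverse event reporting and harms {22}) against Table 3.**

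| Safety endpoint | Window | Visits 3–5 | Month 12 | Month 24 |
|---|---|---|---|---|
| Grade ≥3 complications | 30 days | yes | no | no |
| Seroma | 30 days | yes | no | no |
| Haematoma | 30 days | yes | no | no |
| Superficial or deep SSI | 1 year | yes | yes | no |
| Enterocutaneous fistula | 24 months | yes | yes | yes |
| Revision surgery | 24 months | yes | yes | yes |

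The windows and the table agree with each other. The gap is in scope and is not a contradiction.

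**Step 2. Endpoints still open over time.**
- To day 30: 6 of 6.
- Day 31 to 1 year: 3 of 6, of which two (SSI, fistula) do not require an operation.
- 1 year to 24 months: 2 of 6, of which one (fistula) does not require an operation.

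**Step 3. Length of the gap.** Taking 24 months as 730 days: 730 − 30 = 700 days, and 700/730 = 95.9% of follow-up. This is a share of time. It says nothing about the share of events.

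**Step 4. Test cases.**
- *Uninfected seroma drained percutaneously in week 7 (days 43–49).* It is outside 30 days, not an SSI, not a fistula and not plainly a revision surgery. No explicit route.
- *Readmission in month 3 for a closure-site problem, managed without surgery, infection or fistula.* No explicit route.
- *Mesh infection after month 12 managed without surgery.* The SSI window has closed. No explicit route.
- *Seroma that becomes infected within a year.* Can be recorded as SSI.
- *Late haematoma that is surgically re-explored.* Plausibly a revision surgery, recorded to 24 months.

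**Step 5. Capture outside the safety list.** Chronic pain, quality of life and the modified Hernia Recurrence Inventory are collected at 12 and 24 months, and hernia repair to 24 months. Death without prior hernia and re-laparotomy at the closure site are intercurrent events, to be described by group. None of these identifies a drained collection, a non-operative re-intervention or a readmission.

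**Step 6. What reaches the DSMB.** Its advice rests on surgical site occurrences and on grade ≥3 complications within 30 days. The only components of surgical site occurrences that run past day 30 are SSI and fistula, so the cases without a route in Step 4 do not reach the DSMB either.

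**The case against.** **The windows are deliberate.** The authors lengthened SSI, fistula, revision surgery and hernia repair where they saw a reason. They also explain the absence of SAE recording: the interventions are routine and the trial runs under §15 of the medical professional code. This stands as an account of their choice. It does not supply a route for the cases in Step 4.

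**A fuller document may fill the gap.** The full protocol and the eCRF are not shown, and the article does not define revision surgery, so a site might count percutaneous drainage under it. That is possible. But the article states outright that the six endpoints stand in place of SAE recording, and Table 3 agrees with them. An addition would have to go beyond those statements.

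**There is no evidence of a late difference.** The earlier randomised trial of a biological mesh, as summarised in the Introduction, found no significant difference in wound infection, seroma or serious adverse events. That is fair, although the mesh type and position differed. It is why the point concerns an undetectable harm and claims no likely one.

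**Visit timing.** A reader might infer that a visit on days 30–35 contradicts endpoints that close at day 30, since five of its six permitted days fall after the window. The documents do not support this. A visit that closes a 30-day endpoint has to fall on or after day 30 and looks back over the window. Grade ≥3 complications can normally be dated, and so can haematomas, which by definition warrant exploration and intervention. Only a seroma first seen on days 31–35 lacks a stated counting rule. That is minor, applies to both arms alike, and is settled by recording a date.

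**Conclusion.** The point holds as a gap in scope. In this article, non-operative closure-site complications after day 30 have no explicit recording route unless they are superficial or deep SSI (to 1 year) or enterocutaneous fistula (to 24 months). This covers about 700 of 730 days of follow-up. The number of events involved cannot be derived from the document. The conclusion assumes that the full protocol and eCRF add no further item, and that percutaneous or endoscopic procedures do not count as revision surgery.

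Two stronger readings are not supported:
- *Late harms are recorded nowhere.* Pain, quality of life, hernia repair, revision surgery and deaths without prior hernia are all captured.
- *The 30-day comparisons are biased towards no difference.* A 30-day rate is valid for its own window, and leaving out a day-49 event limits what it covers without distorting it. The loss is that a late excess in the mesh arm, if there is one, would be seen neither by the trial nor by the DSMB.

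This is a cheap improvement. The primary endpoint and the sample size are unaffected.

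**What to change.** Keep the fixed 30-day endpoints, and record the event date or, for a finding such as seroma, the date of first detection. Do not move the end of the window to visit 5, because it would then differ between patients.

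At visits 6 and 7, add two eCRF items, identical in both arms:
1. fluid collection at the closure site, yes or no, on the examination or imaging already done for hernia assessment;
2. any re-intervention (including percutaneous or endoscopic) or readmission for a closure-site complication since the last visit, with its date.

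Report both by group as separate descriptive late-safety lines, apart from the 30-day rates, and include them in the twice-yearly DSMB reports.

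The cost is slightly more data entry and some recall error over the long intervals between visits. No new visit or imaging is needed.

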**Fig. 1 Fig1:**
[figure not shown]
Flow chart. IC, informed consent; POD, postoperative day; POM, postoperative month

**Table 3 Tab3:** Trial visits

Activity	Visit 1 (screening)	Visit 2 (surgery, randomisation)	Visits 3–5 (PODs 2–4, discharge, POD 30–35)	Visits 6–7 (POMs 12, 24)
**Inclusion/exclusion criteria**	x			
**Informed consent**	x			
**Medical history**	x			
**Clinical examination**	x			
**Surgery**		x		
**Randomisation**		x		
**Incisional hernia assessment**^**a**^				x
**Assessment of postoperative morbidity**^**b**^			x	
**Assessment of superficial and deep SSI**^**c**^			x	x (not at POM 24)
**Assessment of wound seroma**			x	
**Assessment of wound hematoma**			x	
**Assessment of enterocutaneous fistula**			x	x
**Incisional hernia repair at the site of ileostomy**			x	x
**Assessment of revision surgery**			x	x
**Pain assessment**^**d**^	x			x
**Health-related quality of life assessment**^**e**^	x			x
**Modified Hernia Recurrence Inventory**^**f**^				x

*POD* postoperative day, *POM* postoperative month, *SSI* surgical site infection

^a^Via blinded assessor: clinical and radiologic assessment

^b^According to Dindo-Clavien classification ≥ 3

^c^Via blinded assessor, according to CDC definition [29]

^d^Measured via the Pain Questions of the EHS-QoL questionnaire [32]

^e^According to the modified EHS -QoL questionnaire [32]

^f^Using the modified Hernia Recurrence Inventory [26]

### Sample size {14}

Sample size calculation is based on the rate of the primary endpoint (IH rate) within 24 months after surgery. Based on the assumption that the percentage of patients developing an IH in the control group is 30% (4–7), we hypothesise a reduction to 15% in the intervention arm (conservative reduction rate below that reported in the above-mentioned trials). Consequently, a sample size per group of 121 patients is needed for the group comparison by the chi-squared test to achieve 80% power in detecting this difference in IH rate at a two-sided level of significance of 5%. It is assumed that using a logistic regression model adjusting for IH risk (low-risk vs. high-risk patients: BMI ≥ 27) and including centre as a random effect in the primary analysis will lead to less unexplained variance and thus to an increased power.

The intercurrent event re-laparotomy affecting the loop ileostomy closure site and death without prior observation of IH are expected to be very rare, with just a few patients each. Based on previous trials, to account for the loss of information, a rate of 20% of dropouts, loss to FU and relevant ICEs (handled with the hypothetical strategy) is considered. Therefore, a total of 304 patients (152 per group) will be randomised. The other ICEs are ignored in the primary estimand and not accounted for in the sample size calculation. Calculation was performed using PASS 16.0.12. Only high-volume trial sites committing to include at least 10 patients per year will be chosen as trial sites.

### Recruitment {15}

To enrol the required number of patients in the planned recruitment period, 13 trial sites will participate in this trial. The trial will be performed by the Clinical Trial Network of the German Society of Surgery (CHIR-Net, www.chir-net.de). The CHIR-Net has successfully performed trials with similar indications and recruitment rates. All trial sites have already successfully participated in surgical clinical trials and have the necessary expertise, equipment and personnel to perform this trial. Participating centres have an estimated annual case load greater *n*=500, ensuring that recruitment should be feasible within the planned recruitment time. It is aimed to minimise loss to follow-up by a pragmatic trial design with high-external validity and financial reimbursement of travel costs for patients covering additional costs for trial-specific visits.

In order to minimise loss to follow-up, the following measures are being implemented:A pragmatic trial design with high-external validity, meaning that trial sites will have little problems to adapt their standard clinical workflow to the follow-up visitsFinancial reimbursement of travel costs for patients covering additional costs for trial-specific visitsAll trial sites are trained in performing surgical clinical trials (CHIR-Net) and have successfully participated in similar trials

Only high-volume trial sites committing to include at least 10 patients per year will be chosen as trial sites.

## Assignment of interventions: allocation

### Sequence generation {16a}

To ensure equal distribution of patient characteristics, randomisation will be used. Allocation of treatments will be performed using a web-based randomisation tool (www.randomizer.at). Block-wise randomisation will be conducted. Randomisation will be stratified by centre.

### Concealment mechanism {16b}

Allocation concealment will be ensured as the result of the randomisation will be unknown to the study team until the patient has been randomised through the web-based tool. Block size will be kept confidential to the study team. Randomisation will be performed in the operation theatre, after the closure of the posterior rectus sheath/posterior fascia. This prevents potential bias by different intraoperative techniques. Before randomisation, the surgeon needs to rule out an infected/septic surgical site (risk for surgical site occurrences (SSO) of grade 4 according to Ventral Hernia Working Group (VHWG) classification) [28].

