### Intervention description {11a}

#### Experimental intervention

The re-establishment of intestinal continuity will be achieved by either stapled or by hand-sewn anastomosis, according to the surgeon’s preference, and the bowel will be positioned back into the peritoneal cavity.Changing of surgical gloves must be performed before mesh implantation. Either after surgical stoma closure or, latest, before mesh placement.A retromuscular space is created by blunt dissection overlapping the suture line in cranio-caudal direction by 4–6cm. In the medial-to-lateral direction, the dissection is limited by the linea alba and linea semilunaris in case the stoma is placed within the rectus sheath. In case the stoma is outside the rectus sheath or below the linea arcuata (no posterior rectus sheath), a retromuscular space should be formed by dissection overlapping the future fascial suture line by 4–6cm in all directions.The posterior rectus sheath (if the stoma is within the rectus sheath) will be closed with a continuous polydioxanone suture (PDS Plus, USP 2-0) with tissue bites of 5 mm and intersuture spacing of 5 mm applied exclusively to the fascia omitting subcutaneous fat and muscle tissue (small-stitch technique, SST). In case the stoma is outside the rectus sheath or below the linea arcuata (no posterior rectus sheath), the posterior abdominal wall should be closed with a continuous polydioxanone suture (PDS Plus, USP 2-0) with tissue bites of 5 mm and intersuture spacing of 5 mm applied exclusively to the fascia omitting subcutaneous fat and muscle tissue (small-stitch technique, SST).The retromuscular space should be irrigated with 500 ml of sterile fluid (lavage) before mesh placement. The type of solution is at the discretion of the surgeon, e.g. saline solution (NaCl 0.9%), Ringer’s or any antiseptic solutions like polyhexanide (PHX), Lavanox or others can be used for this purpose as long as its application is approved for this purpose.A non-absorbable, macro-pore (pore size ≥ 1000μm [23] or effective porosity >0% [24]) light-weight monofilament (class Ia) or mixed structure (class Ic) mesh [24] is placed in the retromuscular position. The size of the mesh should overlap the suture line of the posterior rectus sheath by 4–6cm on all sides. In the medial-to-lateral direction, the mesh size might be limited by the linea alba and linea semilunaris (medial and lateral walls of the rectus sheath). To avoid any commercial interest of a single company, no specific mesh, but rather a well-described uniform CE-certified mesh class must be used in this trial. The safety of this class of meshes has already been shown in prospective trials in abdominal wall repair and ostomy formation [15].The mesh should be fixed to the posterior fascia tension-free with single knots if deemed necessary by the operating surgeon. The suture material is at the discretion of the operating surgeon.The rectus muscle should *not* be closed/approximated by sutures.The anterior rectus sheath will be closed in the same manner as the posterior sheath with a continuous polydioxanone suture (PDS Plus, USP 2-0) with tissue bites of 5 mm and intersuture spacing of 5 mm applied exclusively to the fascia omitting subcutaneous fat and muscle tissue (small-stitch technique, SST).Subcutaneous drains can be placed at the discretion of the operating surgeon.The skin will be closed according to the surgeon’s preference (suture, staples, pursestring).Further perioperative and postoperative treatment will be equal for both groups according to the respective local standard of care.

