
#### Control intervention

The re-establishment of intestinal continuity will be achieved either by staples or by hand-sewn anastomosis, according to the surgeon’s preference, and the bowel will be positioned back into the peritoneal cavity.Changing of surgical gloves.The posterior rectus sheath (if the stoma is within the rectus sheath) will be closed with a continuous polydioxanone suture (PDS Plus, USP 2-0) with tissue bites of 5 mm and intersuture spacing of 5 mm applied exclusively to the fascia omitting subcutaneous fat and muscle tissue (small-stitch technique, SST). In case the stoma is outside, the rectus sheath or below the linea arcuata (no posterior rectus sheath), the posterior abdominal wall should be closed with a continuous polydioxanone suture (PDS Plus, USP 2-0) with tissue bites of 5 mm and intersuture spacing of 5 mm applied exclusively to the fascia omitting subcutaneous fat and muscle tissue (small-stitch technique, SST).The rectus muscle should *not* be closed/approximated by sutures.The *anterior* rectus sheath will be closed with a continuous polydioxanone suture (PDS Plus, USP 2-0) with tissue bites of 5 mm and intersuture spacing of 5 mm applied exclusively to the fascia omitting subcutaneous fat and muscle tissue (small-stitch technique, SST).Subcutaneous drains can be placed at the discretion of the operating surgeon.The skin will be closed according to the surgeon’s preference (suture, staples, pursestring).Further perioperative and postoperative treatment will be equal for both groups according to the respective local standard of care.

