## Assignment of interventions: blinding

### Who will be blinded {17a}

Blinding will be performed according to the evidence-based guidelines published by Probst et al. [33].A.Patients are blinded as they are under general anaesthesia during the trial intervention. Neither the discharge letter nor the operation report will contain any information regarding group allocation. This will be monitored by the clinical monitor.B.Surgeons performing the operation are unblinded to the trial intervention. To minimise performance bias, randomisation is performed after the closure of the posterior wall of the abdomen.C.For blinded outcome assessment, the person performing randomisation and the surgical team conducting the control/experimental intervention (“unblinded” study members) will be documented. All outcome assessments must be performed by blinded clinical assessors *not* being part of this group. This must be documented and will be verified by the clinical monitor.D.The trial statistician is blinded as she/he has no access to unblinded data during the study. Furthermore, the statistician will perform according to a pre-defined statistical analysis plan which will be finished prior to database closure.E.For primary endpoint evaluation, a clinical as well as radiological examination needs to be performed. Clinical outcome assessment must be performed by a surgeon. Blinding the radiologic examination can be achieved easily, as these physicians are not part of the prior trial interventions or the clinical trial centre. For clinical evaluation, the same prerequisites apply as outlined above, i.e. surgeons performing the clinical evaluation must be independent of the “unblinded” trial team.

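### Randomisation is placed after posterior closure, but the mesh arm's retromuscular dissection is listed before that closure and the control arm lists none: the three statements cannot all hold

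*Protocol article*

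**What the plan says.** All references are to the protocol article.

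- **Point of allocation.** Concealment mechanism {16b}: "Randomisation will be performed in the operation theatre, after the closure of the posterior rectus sheath/posterior fascia". The reason follows: "This prevents potential bias by different intraoperative techniques". Who will be blinded {17a} repeats the timing: "To minimise performance bias, randomisation is performed after the closure of the posterior wall of the abdomen".
- **Mesh arm.** The Experimental intervention list runs: anastomosis, glove change, retromuscular dissection, posterior closure, lavage, mesh placement, anterior closure. For a stoma within the rectus sheath, the dissection item reads: "A retromuscular space is created by blunt dissection overlapping the suture line in cranio-caudal direction by 4–6cm". For a stoma outside the sheath or below the linea arcuata: "a retromuscular space should be formed by dissection overlapping the future fascial suture line by 4–6cm in all directions". Posterior closure is the next item.
- **Control arm.** The Control intervention list passes directly from glove change to posterior closure: "Changing of surgical gloves.The posterior rectus sheath (if the stoma is within the rectus sheath) will be closed with a continuous polydioxanone suture". No retromuscular dissection appears anywhere in it.

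Nothing in the article says that every patient is dissected before allocation, or that the mesh-arm steps may be taken in another order.

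**The concern.** By the mesh-arm list, the dissection falls due at a moment when, by the allocation sections, nobody yet knows the patient's arm. A surgeon cannot follow both arm descriptions and the allocation rule.

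What is at stake is the meaning of the comparison. If the dissection belongs to the mesh arm only, the hernia difference estimates mesh plus dissection against closure. If everyone is dissected, it estimates the addition of mesh given dissection in both arms, and the comparator is no longer the standard closure alone named under Objectives {7}. The treatment attribute of the primary estimand (Statistical methods {20a}) does not mention dissection, so it does not settle which is meant.

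Safety is affected in the same way. Seroma, haematoma and surgical site infection are components of the surgical site occurrence endpoint, serve as safety measures and inform the DSMB's advice. Any such events caused by the dissection would show up as a difference between arms under one reading and be common to both arms under the other. The per-protocol rule may not pick this up, because the technical aspects it names are suture material, stitch technique and mesh used, not dissection.

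**Working it through.** The question is one of order, so no figure in the plan has to be reproduced. The sample size (121 per group; 121 / (1 − 0.20) = 151.25, rounded up to 152; 2 × 152 = 304) does not involve the step order and is unaffected.

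**The three statements**

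| | Statement | Section |
|---|---|---|
| A | Randomisation comes after posterior closure | Concealment mechanism {16b}; Who will be blinded {17a} |
| B | Mesh-arm dissection comes before posterior closure | Experimental intervention |
| C | Controls have no retromuscular dissection | Control intervention |

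**Why they conflict**

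1. From B, dissection precedes posterior closure. From A, posterior closure precedes randomisation. So dissection precedes randomisation.
2. Before randomisation the arm is unknown, so the dissection cannot be reserved for those who will later be allocated to mesh.
3. B requires every future mesh patient to have had it. Therefore every patient about to be randomised must have had it, including future controls.
4. That contradicts C.

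**Giving up one statement at a time**

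| Given up | What happens | Comparison obtained | Safeguard against performance bias |
|---|---|---|---|
| C | All patients are dissected, then closed posteriorly, then randomised | Mesh versus no mesh, with dissection in both arms | Holds: every step before allocation is the same |
| B | Posterior closure, randomisation, then dissection in the mesh arm only | Mesh plus dissection versus closure | Holds: anastomosis and posterior closure are done with the arm unknown |
| A | Allocation is known before dissection | Mesh plus dissection versus closure | Lost: posterior closure is done with the arm known |

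The third row is excluded by two sections of the article. The first two rows are the live readings. Each contradicts one of the two arm descriptions.

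**How firm is B?** For stomas outside the sheath or below the linea arcuata, the dissection is set out relative to a suture line still to be made ("a retromuscular space should be formed by dissection overlapping the future fascial suture line"), and the list position agrees. For stomas within the sheath, the wording ("A retromuscular space is created by blunt dissection overlapping the suture line in cranio-caudal direction") does not say whether the line already exists, so B rests there on list position alone.

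**The case against.** The strongest reply is that the mesh-arm list is not a strict chronology. Its glove-change item comes second, yet it may be done as late as just before mesh placement, that is, after items listed below it. The item numbering was lost when the text was extracted. For a stoma within the sheath, the wording is compatible with a posterior suture line already in place. Even where the line is described as still to come, the phrase says fascial and does not name the posterior layer. Surgeons must also pass eLearning tutorials on both closures, the eCRF asks for protocol deviations, and the article condenses a fuller protocol.

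Part of this stands. It limits the certainty for within-sheath stomas, and the training may already fix one order. It does not remove the conflict. The glove-change item states its own flexibility and the dissection item states none. The list position and the wording about a future line point the same way, and no sentence in the article reconciles the sections. This is a contradiction between things the article states, not a detail left out of it.

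Two stronger readings are tempting and are not supported. A reader might infer that the claimed protection against performance bias fails whichever way a site resolves the conflict. It does not: it holds if all patients are dissected before allocation, and it holds if dissection follows allocation. It would be lost only if the arm became known before the dissection, which both allocation sections exclude. A reader might also infer that all 304 patients, or all 152 controls, are affected. Those figures are the planned sample and are only upper bounds; nothing in the article shows that any control was dissected or that sites differ in practice.

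**Conclusion.** Wrong as written. The point of allocation and the two arm descriptions cannot all be followed, and the article leaves open whether controls undergo retromuscular dissection. The content of the comparator, and what the hernia and surgical site occurrence comparisons estimate, are therefore not fixed.

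The conclusion assumes that the listed sequence of dissection and closure is meant as the operative order. That is well supported for stomas outside the sheath or below the linea arcuata, and is an inference from list position for the rest. Neither the number of patients concerned nor the size of any effect on event rates can be derived from the document. Concealment, the intention-to-treat analysis, the primary endpoint and blinded outcome assessment are not called into question.

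**What to change.** 1. Reconcile Experimental intervention, Control intervention, Concealment mechanism {16b} and Who will be blinded {17a} into one step order. Every step before randomisation should be listed identically in both arms, and every arm-specific step should come after it. Which operative sequence is right is for the investigators to decide.
2. Check that the eLearning tutorials show that same order, and update them if they do not.
3. Add eCRF items on whether retromuscular dissection was done and whether it came before or after allocation, and report them by arm. If dissection turns out to be specific to one arm, these items reveal the allocation and must be kept from the blinded assessors.
4. Recruitment began in October 2022, so complete the same items for patients already operated on, as far as the unblinded team can document them.

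The cost is a protocol clarification, possibly a training update, and one or two eCRF items. No extra patients are needed and the planned analysis model does not change.
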